### Stratification of results

Clinical outcomes will be stratified according to the minimization criteria. The Data and Safety Monitoring Board (DSMB) will regularly verify that subgroup treatment outcomes are within the confidence intervals of the study hypotheses.

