### Primary hypothesis of ISAT II

Endovascular management of patients with ruptured, intradural, intracranial aneurysms suitable for both endovascular and surgical management, for whom the treating physician remains unsure whether the results of the original ISAT study apply, will lead to a decrease in the number of poor outcomes (defined as modified ranking scale (mRS) >2) from 30% to 23% at one year.

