### Number of patients

With target alpha 0.05 and power 90%, a sample size of 1,724 patients (862 per group, no losses) would be sufficient to demonstrate a significant difference, using estimated 23% and 30% poor clinical outcome rates for endovascular treatment (EVT) and surgical management at one year, respectively (two-sided Fisher’s exact test). We expect very few losses to follow-up (<10%), and the target sample size is 1,896 patients.

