### Planned analyses

The main statistical tests will involve comparisons between the probability of reaching the primary end-point (dependent survival or death at one year) with a surgical or endovascular management strategy. Descriptive statistics will be done on demographic variables and potential risk factors to compare the two groups at baseline. Means, standard deviations, and ranges will be presented for quantitative variables such as size of aneurysms and frequency tables for categorical variables (such as the number of patients with multiple aneurysms). Statistics will be broken down by center and by treatment arm. Comparison of the groups will be assessed through independent ANOVA (quantitative data) or Mantel-Haentzel and *χ*^2^ tests (categorical data). Assuming comparability of groups across centers, the primary outcome will be compared between groups using a Fisher’s exact test at one year.

Secondary outcomes will be compared using independent *t*-tests for quantitative variables and *χ*^2^ tests for categorical variables. The analyses of follow-up data will control for baseline data using logistic regression, ANCOVA or Cox regression multivariate methods. All tests will be interpreted with a 0.05 level of confidence.

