### A single large trial or multiple small trials

One of the difficulties specific to our field is the relatively small number, and heterogeneity of patients with rup-tured intracranial aneurysms, which renders well-powered randomized studies addressing specific questions difficult to complete. To mitigate this difficulty, in the spirit of the original ISAT study, we have chosen to keep inclusion criteria broad. This choice of study design has two implications: the first is that at best, a general answer to the question will be obtained, which can, at some future time, be refined by other studies with more narrow inclusion criteria. Although the overall number of patients for whom the uncertainty persists is quite large (perhaps in the range of 40% or more), the reasons why these patients are not typical original ISAT cases are multiple and various. For some clinicians, each individual reason (ie: giant aneurysms, very small aneurysms) could be considered as distinct research questions, and that ISAT-II combines heterogeneous groups that they judge should not be lumped into an overall outcome result, for fear of averaging results that would normally pull in opposite directions. There may be no universally acceptable answer to this problem. Others may fear that by the sheer force of the law of large numbers differences in study population may not be clearly highlighted in demographic statistics or results and we may end up simply ‘repeating ISAT’. Except for depriving patients from a treatment that would have already been shown superior in a previous trial, a possibility that is explicitly excluded in the objectives and hypotheses of ISAT II, what this concern amounts to in actual practice remains unclear. We must, however, remember the first goal of care trials: to protect present patients from unjustified beliefs and hypotheses, and offer optimal care in the presence of uncertainty [[name], [name], Altman DG: Introducing care trials. J Clin Epidemiol 2012. Provisional acceptance]. From an organizational perspective, it is easier to propose a single inclusive large trial than to multiply small trials with narrow selection criteria. It is possible, though, to pre-specify subgroups that will separately be monitored by the DSMB. Thus, the second implication of the ISAT II design choice is that the DSMB must regularly be provided with subgroup-specific safety data to ensure that an emerging obvious discrepancy in clinical outcome will be addressed in a timely manner in order to prevent additional patient morbidity. A randomized context is the only way to firmly establish that one particular treatment modality ought not to continue to be offered to a particular subgroup of patients.

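### The DSMB's subgroup check measures outcomes against the hypothesised 23% and 30% instead of comparing the arms within each subgroup, so it does not serve its stated purpose

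*Protocol article*

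**What the plan says.** The section Stratification of results has two sentences. The first defines the strata: "Clinical outcomes will be stratified according to the minimization criteria". The second gives the DSMB its task: it "will regularly verify that subgroup treatment outcomes are within the confidence intervals of the study hypotheses".

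The hypotheses are point rates. Primary hypothesis of ISAT II states a fall in poor outcome (mRS above 2) "from 30% to 23% at one year". Number of patients repeats the two rates: "using estimated 23% and 30% poor clinical outcome rates for endovascular treatment (EVT) and surgical management at one year, respectively". The article gives no confidence interval for either rate or for their difference. Nor does it give a level, a sample size for the interval, or a statement of whether the check applies to arm rates or to the difference.

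The purpose appears in the Discussion, under A single large trial or multiple small trials: "the DSMB must regularly be provided with subgroup-specific safety data to ensure that an emerging obvious discrepancy in clinical outcome will be addressed". There, subgroup monitoring is presented as a consequence of the choice to pool heterogeneous patients in one trial.

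**The concern.** The minimization factors are age 70 or over, WFNS grade above 3, aneurysm size of 10 mm or more, and posterior circulation location. The article's own justification of these factors says that older patients do worse under either treatment, that SAH grade predicts outcome, and that posterior location carries a worse prognosis with both treatments. For size it speaks of treatment risk and recurrence. Subgroups formed on the first three factors should therefore differ from 23% and 30% in both arms, whatever the treatment effect.

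A check against those two fixed rates mixes baseline risk with treatment effect. A flag may show only that the patients were sicker, and no flag does not show that the arms are in the expected order. At stake is the safeguard that the Discussion attaches to broad inclusion. The authors themselves regard a reversed effect as possible, since they cite a potential benefit of surgery over age 70 (RR 1.15, 0.82 to 1.61).

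**Working it through.** **Inputs from the article:** 23% and 30% poor outcome; "With target alpha 0.05 and power 90"%; "two-sided Fisher’s exact test"; 862 per group.

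**Assumptions (the article gives no figures):** 95% intervals of the form p ± 1.96·√(p(1−p)/n); subgroup sizes of 50 to 200 per arm; a poor-prognosis subgroup with 48% v 55% and a good-prognosis subgroup with 13% v 20% (both keep the 7-point benefit); a reversal of 30% v 23%. All pairs are endovascular v clipping.

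**1. The plan's own figure.** n₀ = [1.960·√(2·0.265·0.735) + 1.282·√(0.23·0.77 + 0.30·0.70)]² / 0.07² gives 834 per arm. The continuity correction, (n₀/4)·[1 + √(1 + 4/(0.07·n₀))]², gives 862, as stated. Exact Fisher power at 862 per arm is 90.1%. The sample size is not in question.

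**2. Per-arm reading, intervals at subgroup size.** A subgroup passes if both observed rates lie inside their intervals, so P(pass) is the product of two binomial probabilities. At 100 per arm:
- Endovascular: 23 ± 1.96·4.21 = 14.8 to 31.2
- Clipping: 30 ± 1.96·4.58 = 21.0 to 39.0
- Largest reversal that fits: 31.2 − 21.0 = 10.2 points

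| n per arm | Endovascular interval | Clipping interval | Largest passing reversal | 23 v 30 passes | 48 v 55 passes | 13 v 20 passes | 30 v 23 passes |
|---|---|---|---|---|---|---|---|
| 50 | 11.3–34.7 | 17.3–42.7 | 17.4 | 92% | 0.1% | 45% | 66% |
| 100 | 14.8–31.2 | 21.0–39.0 | 10.2 | 90% | about 0% | 11% | 40% |
| 150 | 16.3–29.7 | 22.7–37.3 | 7.1 | 91% | about 0% | 3% | 27% |
| 200 | 17.2–28.8 | 23.6–36.4 | 5.2 | 90% | about 0% | 0.4% | 14% |

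The two intervals overlap until 606 per arm. A poor-prognosis subgroup with the effect reversed (55% v 48%) also passes about 0% of the time at 100 per arm. In such a subgroup the flag is the same whether the planned benefit is present or reversed.

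**3. Per-arm reading, intervals fixed at 862 per arm.** Endovascular: 23 ± 1.96·1.43 = 20.2 to 25.8. Clipping: 30 ± 1.96·1.56 = 26.9 to 33.1. Because 25.8 is below 26.9, no observed reversal can pass. But a subgroup with true rates of exactly 23% and 30% passes only 25% of the time at 100 per arm and 44% at 200, so most flags in subgroups of that size would be chance or prognosis.

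**4. Difference reading.** The interval is 7 ± 1.96·√((0.23·0.77 + 0.30·0.70)/n) points. At 100 per arm this is 7 ± 12.2, or −5.2 to 19.2. The 48% v 55% subgroup now passes 92% of the time. The reversal of 30% v 23% still passes 40% of the time at 100 per arm and 12% at 200. The interval includes zero below 304 per arm. Fixed at 862 per arm it is 2.8 to 11.2 points; an observed reversal fails, but a 100-per-arm subgroup exactly as hypothesised passes only 53% of the time.

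**The case against.** **The sentence may mean the difference.** The hypothesis is worded as a decrease, and the Discussion's aim is plainly between-arm. This is fair, and on that reading the prognosis problem largely disappears. What remains is step 4: with subgroup-size intervals a reversal can pass, and with the fixed interval nearly half of 100-per-arm subgroups behaving as planned are flagged.

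**This is a condensed article.** The full protocol or a DSMB charter may set the schedule, level and boundaries, and their absence here is no finding. That stands. The point concerns what the printed sentence does fix, namely the comparator: agreement with the study hypotheses.

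**A reader might infer that the check cannot detect harm.** The figures do not support that. Large harm in an average-risk subgroup would be flagged, and even the 30% v 23% reversal is flagged about 60% of the time at 100 per arm. Nor is every result that passes clear harm: 31/100 v 22/100 lies inside the subgroup-size intervals, but its Fisher p is 0.20.

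**A reader might also infer repeated subgroup testing at the 5% level**, from "All tests will be interpreted with a 0.05 level of confidence". That sentence is under Planned analyses and does not mention the DSMB. The check is not a between-arm test, so no false-signal rate for repeated 0.05 tests can be attributed to it.

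**Conclusion.** The point holds in a limited form. None of the four readings examined gives a sound check of whether one treatment is doing worse in a subgroup. Read per arm, subgroups that the article itself calls prognostic are flagged almost always even with the full benefit, if their rates are as far from 23% and 30% as assumed here; a smaller prognostic gap would be flagged less often. The passing of a reversal depends on intervals computed at subgroup or interim size and on a subgroup with near-average overall risk. It does not occur with intervals fixed at 862 per arm, where the fault is excessive flagging instead. The percentages rest on assumed subgroup sizes, assumed rates and 95% intervals.

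A reader might go further and conclude that the trial's main result is compromised. The documents do not support that: the primary test and sample size are untouched, and the sentence attaches no stopping or exclusion to a flag. The fault is a mismatch between the monitoring criterion and its stated purpose.

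**What to change.** Replace the second sentence of Stratification of results with wording such as: *At each review the DSMB will receive, for each pre-specified subgroup, the between-arm risk difference in poor outcome with its confidence interval and the treatment-by-subgroup interaction. Possible harm will be judged on this comparison and not on agreement with the planning rates of 23% and 30%.*

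Leave any numerical signal threshold to the DSMB charter, because the choice is a trade-off. For example, a p<0.001 trigger would flag a true 31% v 22% at 100 per arm only about 3% of the time, against about 70% under the present check with 100-per-arm intervals.

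The cost is a change of wording; the DSMB needs no data beyond the subgroup outcomes already planned for it. The downside is imprecision. At 100 per arm a difference near these rates carries about ±12 points, so the DSMB must use judgement and not read any single subgroup interval as decisive.

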### Ethics approval

The Health Research Ethics Board of the University of Alberta approved the protocol on October 1^st^, 2012 (Study ID: Pro00032613), the Institutional Review Board of the Centre Hospitalier de l’Université de Montréal approved the protocol on October 22^nd^, 2012 (Study ID: 12.136). Secondary approval will be sought from all local ethics committees. Based on the Declaration of Helsinki, written informed consent will be obtained from each participating patient or appropriate surrogate in oral and written form prior to enrollment. The ISAT II study is registered with ClinicalTrials.gov: NCT01668563.

## Discussion

In many centers, the consequences of the positive results of the original ISAT study was that endovascular ruptured aneurysm treatment was given the right of first refusal for all aneurysms, and all patients. Proponents of endovascular therapy often assert that the technology (and thus outcomes) will have improved since ISAT, which was interrupted more than 10 years ago, for the benefit of all patients. Not only has this never been proven, there is reason to fear that extrapolation of ISAT results to many patients that would not have been included in the original trial could lead to clinical outcomes that may be inferior to surgery. Although we have designed ISAT II as a pragmatic trial, the intent is not to repeat ISAT. Our aim is to provide optimal care to those patients for whom clipping may still be the best option, although this is once more only a hypothesis that must be trialed against the new generalization that coiling, in the majority of patients, provides the best results.

Although pre-randomization, as has been used in the BRAT trial, is possible, we have chosen a classical design, with randomization only after clinicians have considered the patient eligible for both treatment options, explained both alternatives, and obtained inform consent [8]. The issue of ‘equipoise’ that could, if too narrowly understood, excessively limit recruitment is acknowledged, but other designs such as Zelen’s [29] raise additional ethical issues that we preferred to avoid.

### Questions that remain unanswered after ISAT

Patients for whom major uncertainty persists can be defined by using three overlapping categories: i) patients that were excluded from the original ISAT study, for lack of ‘equipoise’ at the time; ii) patients for whom there is an a priori clinical reason to suspect results could be different from overall trial outcomes, but for whom ISAT subgroup analyses could not provide sufficient power to support a definitive conclusion; iii) patients that can now be treated using an endovascular approach as a result of the availability of new devices that were not available at the time of ISAT.

### Patients excluded from ISAT

More than 9,559 aneurysms were screened, but only 2,143 patients were enrolled in the original ISAT study [5]. The applicability of the study results to the type of patients that were screened but excluded remains in doubt. Subgroup analyses show that a variety of aneurysms and clinical situations were under-represented in the original ISAT study [30]. MCA bifurcation aneurysms are readily accessible by surgery, while their anatomy may sometimes be less favorable for simple coiling, at least during the years that ISAT was conducted. MCA aneurysms were likely excluded because they were preferentially clipped. Due perhaps to perceived difficulties with surgical access, an insufficient number of posterior circulation aneurysm (only 2.7% of the total number) were included in ISAT. Posterior circulation aneurysms, and especially basilar bifurcation aneurysms, were likely preferentially coiled [31]. As a result, a substantial number of clinicians remain unsure about the best management of MCA and of non-basilar, posterior circulation aneurysms.

### Patients for whom subgroup analyses remain unconvincing

Subgroup analyses are notoriously potentially misleading [32], however, they can be used to help formulate hypotheses for a new trial, especially when there are a priori reasons to suspect that results in certain subgroups may differ from the overall results.

#### Patient age

Subgroup analyses from ISAT point to an interaction with age (*P* = 0.04), with a potential benefit from surgery in patients older than 70 (RR: 1.15 (0.82, 1.61)). In younger patients, surgeons may be tempted to clip a ruptured aneurysm because the benefits of coiling may be smaller (RR: 0.91 (0.59, 1.39), while clipping may promise a lower risk of recurrence [33]. Younger patients (<40 years of age) have greater remaining life expectancy during which their risk of developing an aneurysm recurrence may be greater, while older patients (>70 years old) may have heightened treatment-related risks with either modality, with increased surgical risks, as well as more difficult and risky endovascular access.

#### Location

Subgroup analyses of ISAT showed an interaction with location (*P* = 0.01). Only 14.1% of aneurysms in the original ISAT were located on the MCA, likely because lesions in this location were preferentially treated surgically. Despite this selection, the subgroup analysis showed similar results for coiling and clipping (RR: 1.01 (0.71, 1.45)). Today, many more MCA aneurysms are coiled, often with adjunctive balloons and stents. Are these patients really better served with endovascular rather than surgical treatment?

#### Aneurysm size

Subgroup analyses of ISAT failed to show an interaction with aneurysm size (*P* = 0.4), and results for aneurysms larger than 10 mm were similar (RR: 0.96 (0.65, 1.42)). The rate of aneurysm recurrence increases as aneurysm size increases [9], and many clinicians are tempted to use stents or to treat large aneurysms with clipping, in spite of the ISAT overall results.

### Patients now treated via an endovascular strategy with new devices

Proponents of endovascular treatment sometimes justify expanding the indications of the endovascular approach on the basis of improved catheter and coil technology, although this presumption has never been reliably demonstrated. The increasing use of stents and, more recently flow-diverters, which were not tested in ISAT, may increase endovascular treatment risks; they require the additional use of a dual anti-platelet agent regimen to prevent subacute thrombotic complications, which can in turn increase risks of re-bleeding and hemorrhagic complications of ventricular drainage [26,34,35]. These devices may expand indications of EVT to wide-neck aneurysms that would not have been included in ISAT. The wider spectrum of patients and aneurysms now considered for EVT may not all experience the benefit seen in the original ISAT trial [6]. The relatively small ARR of 7.4% favoring coiling over clipping may no longer hold when the potential risks due to stents are considered.

Other considerations often influence treatment choices. Certain patients may carry a higher risk with endovascular management: very small (<4 mm) aneurysms [35,36] or wide-neck (>4 mm) aneurysms [26] (or any lesion whose treatment may require a stent) have been shown, in case series, to carry increased risks [26]. For these aneurysms, the relatively small advantage demonstrated in ISAT may not apply to current patients facing the dilemma of trying to choose the best treatment modality. On the other hand, some clinical situations may be more favorable to surgical management. This includes patients presenting with a large but non-life threatening intraparenchymal hematoma, or those with multiple aneurysms accessible through one craniotomy. Many questions regarding when coiling or clipping is appropriate remain, and a number of patients are proposed surgery, despite ISAT, and all without convincing evidence. On the other hand many patients are proposed EVT, using devices that have never shown superiority to clipping. Clinicians are presently forced to make case-by-case decisions based on unreliable estimates of the respective risks and benefits of each intervention. A more prudent, systematic approach is in order. The essence of scientific medicine is to question the hypotheses behind our as-of-yet not validated actions. We believe we need another pragmatic trial, which is the best way to offer the best possible care in the presence of uncertainty [37].

### When should trials be interrupted?

If so much uncertainty remains after ISAT, one may ask, at least in retrospect, why was this successful, international collaboration interrupted? Why did the SAH patient randomization process, finally under way in ISAT, not simply continue? The difficult-to-initiate process of randomizing SAH patients could easily have continued in participating centers, with a more refined question, immediately, for patients for whom the uncertainty persisted. The false notion that trials (presented here as the ethically most acceptable means to deal with patient management uncertainties), must be interrupted as soon as a convincing result is shown for the primary hypothesis, is hopefully a soon-to-be archaic notion that clinical research is foreign to medical care. The problem is that once a trial like ISAT is interrupted, the community of recruiting clinicians goes into hibernation, often for many years, until the momentum is gathered anew to launch another trial to address those questions which emerge as soon as the initial trial results are published. During this quiescent period, non-validated practices and dogmas quickly take over the field, rendering the process of trial initiation fearsomely difficult. We must remember that clinical sciences differ from ‘pure’ sciences, like physics: there are no universal laws; patient outcomes are what matters, and care must constantly be reappraised. The verdict of even a landmark trial does not close the book on the subject matter. On the contrary, it opens the door to multiple, more specific trial-able questions. With this modern vision, properly designed trials would provide optimal care in the presence of uncertainty, and the role of the DSMBs would be modified. Instead of suggesting trial termination, they would suggest interruption only for that one particular question, while pointing out where the line of questioning of the ongoing trial must continue. The current organization of clinical research, which centers on singular questions addressed one by one, should be replaced with a broader enterprise embracing programs of a wider scope and aim. Once a network of centers is well-organized and delivers reliable answers to pertinent clinical questions, it should pursue a more general goal: to provide transparent, optimal clinical care, proposing randomized studies to all patients for whom the results of an up-to-date randomized trial are not available.

